### Sample size

3.8

The study is powered to address Research Question 1a. Previous research indicates an effect size of 0.78 for differences in somatosensory attenuation between young and older individuals (Parthasharathy et al., 2022). Powering the current study to detect an effect size of 0.78 between two independent means for Research Question 1a—somatosensory attenuation in individuals with and without long COVID—with an α error probability of 0.05 and a power of 95% and based on a non‐directional two‐tailed hypothesis requires 44 participants per group (G*power 3.1.9.7). Dropout is not expected to impact Research Question 1a or 1b, as it involves initial measurements during the first session. However, there is a potential for dropout to impact the subsequent research questions, which rely on participants returning for a second session.

The sample size gives us power of 90% to detect an effect of 0.70 between two groups at two repeated time points with alpha error probability of 0.05 for Research Questions 2 and 3, or a power of 80% to detect an effect of 0.60. A dropout rate of 10% would mean that our power to detect these effect sizes decreases to 60%. The approach for addressing Research Questions 2 and 3 ensures that the study is adequately powered to detect correlations of 0.50 and 0.40, respectively. The code used to calculate the outcome measure is available at https://github.com/smancuso/R‐ Code/blob/cc90c623c4dc733fe5c93ef5a795dde010152c63/Power.R

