### Statistical analysis

3.7

A series of statistical analyses will be conducted to compare the descriptive characteristics of the two groups (long COVID/neither long COVID nor fatigue). The characteristics to be compared are age, gender, trait fatigue (FAS score, CFQ‐11 total score, CFQ‐11 physical subscale score, CFQ‐11 mental subscale score), impact of trait fatigue (MFIS physical subscale score, MFIS cognitive subscale score, MFIS psychosocial subscale score), mood (HADS‐A score, HADS‐D score), illness beliefs (BIPQ score), and autonomic symptoms (COMPASS‐31 score). Gender will be analysed as a categorical variable. A chi‐square test will be used to compare the gender distribution between the groups. All other variables will be analysed as ratio data and compared across groups using an independent samples if the data meet parametric assumptions (normality, verifying equal variance) and a Mann–Whitney *U* test if the data do not meet parametric assumptions.

Results will be summarized using a measure of central tendency (mean or median) and spread (standard deviation or interquartile range), test statistics, and *P*‐values for ratio data and frequency, percentage, chi‐square values, and *P*‐values for categorical variables.
Hypothesis 1Pre‐task (baseline) somatosensory attenuation will be different between individuals with long COVID fatigue and controls. We will also attempt to replicate the Baker et al. (2023) finding that somatosensory gating is not different between individuals with long COVID fatigue and controls. The independent variable will be ‘participants’, which consists of two categories: ‘individuals with long COVID fatigue’ and ‘controls’. The two dependent variables will be ‘somatosensory attenuation’ and ‘somatosensory gating’, measured at baseline during the first session participants attend.

This will be tested using a multivariate analysis of variance to test for an overall difference in somatosensory processing between populations, and to explore the differences in somatosensory gating and attenuation. We will check that the following assumptions are met: multivariate normality, independence and equal variance. If we find the multivariate analysis of variance is significant, we will conduct follow‐up univariate analysis of variance for somatosensory attenuation and somatosensory gating to identify specific contributions to the effect and will apply Bonferroni correction to control for the increased risk of Type I error.

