#### Planned exploratory analysis

3.7.1

Hypotheses 1, 2, 3 will be rerun with age included as a covariate.Hypotheses 1, 2, 3, 4 will be rerun with time of day (morning/afternoon) at which participants completed sessions and session order (cognitive/physical first) included as additional predictor variables.The effect of autonomic dysfunction during exertion, on state fatigue pre‐ to post‐exertion, via an effect on somatosensory processing post‐exertion will be tested using mediation analysis with separate models for somatosensory attenuation and somatosensory gating. This will be quantified in participants with and without long COVID.The relations between autonomic dysfunction during exertion, state fatigue during exertion, and perceived effort during exertion will be quantified in participants with and without long COVID during both tasks (cognitive/physical). This will be tested using correlation analysis.Test‐retest reliability will be conducted for each somatosensory processing measure (gating and attenuation), from the baseline measure from each session (cognitive/physical). This will provide a measure of whether somatosensory processing is stable over time.

We will carry out outcome neutral criteria that must be met for successful testing of the stated hypothesis. This includes checking for the absence of floor or ceiling effects. This will be done by examining data distributions to ensure that there are no extreme values that could impact the validity of results. Additionally, we will investigate the quality of the data and this will include frequency measures and the shape of the distribution.

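### The 95% power stated for Research Question 1a belongs to a single t-test at 0.05; the planned MANOVA followed by Bonferroni-corrected tests has about 90%

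*Protocol article*

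**What the plan says.** Section 3.8 (Sample size) names the question that drives the size of the study: "The study is powered to address Research Question 1a". It describes the calculation as "Powering the current study to detect an effect size of 0.78 between two independent means", "with an α error probability of 0.05 and a power of 95" per cent, and concludes that a "two‐tailed hypothesis requires 44 participants per group". This is a single two-sample t-test on attenuation.

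Section 3.7 (Statistical analysis, Hypothesis 1) tests the same question differently. Attenuation and gating enter a two-outcome MANOVA. The separate analyses of variance depend on its result: "If we find the multivariate analysis of variance is significant, we will conduct" the univariate follow-up. For those follow-up tests the authors "will apply Bonferroni correction to control for the increased risk of Type I error". The same section says the authors hope to replicate a published result that gating does not differ between the groups.

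**The concern.** Two sections of one document describe different tests for the one question the study is sized for. The sample size section allows neither for the condition that the MANOVA be significant first nor for the smaller alpha of the follow-up test. Both steps can only lower the chance of declaring an attenuation difference. They also tie that chance to gating, an outcome on which the authors expect no effect.

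What is at stake is how a negative result is read. Section 3.9 (Timeline) shows that this is a registered report with a Stage 2 submission to follow, so a null attenuation finding will be weighed against the advertised 95%. If the planned procedure has about 90%, the risk of missing a true effect of 0.78 is about 10%, twice the 5% that readers are told.

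**Working it through.** **Inputs from the protocol article.** Standardised difference d = 0.78; n = 44 per group; two-sided alpha 0.05; power 95% (Section 3.8). Two outcomes, MANOVA first, then Bonferroni-corrected univariate tests (Section 3.7).

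**Assumptions, because the document does not print them.** MANOVA alpha 0.05 (the only alpha the document gives). Bonferroni divisor 2, since two follow-up tests are named, so 0.05/2 = 0.025 each. Gating difference 0 as the base case, in line with the authors' expectation. Within-group correlation r between attenuation and gating varied from −0.5 to 0.5.

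**Step 1: the plan's own figure.** Two-sample t-test, degrees of freedom 2 × 44 − 2 = 86, noncentrality d√(n/2) = 0.78 × √22 = 3.659. The two-sided critical value at 0.05 is 1.988. The noncentral t distribution gives power 95.1% with 44 per group and 94.7% with 43. The stated 44 per group is reproduced.

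**Step 2: the Bonferroni step alone.** Same noncentrality, alpha 0.025, critical value 2.281: power 91.4%. Reaching 95% at this alpha needs 51 per group (95.03%; 50 per group gives 94.6%). Put the other way, 44 per group has 95% power at 0.025 for d = 0.84 instead of 0.78.

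**Step 3: the MANOVA alone.** With two groups this is Hotelling's T². For a gating difference of 0 the noncentrality is (n/2) × d²/(1 − r²) = 22 × 0.6084/(1 − r²), and F has 2 and 85 degrees of freedom. For r = 0 the noncentrality is 13.38 and power is 90.6%. For r = ±0.3 it is 14.71 and 93.1%. For r = ±0.5 it is 17.85 and 96.9%.

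**Step 4: the planned procedure.** Probability that the MANOVA is significant at 0.05 and attenuation is significant at 0.025, by simulation (2,000,000 replicates per row), gating difference 0:

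| r | MANOVA | Attenuation at 0.025 | Both |
|---|---|---|---|
| 0 | 90.6% | 91.4% | 89.4% |
| ±0.3 | 93.1% | 91.4% | 90.2% |
| ±0.5 | 96.9% | 91.4% | 91.0% |

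Allowing gating differences of 0.3 and 0.78 as well (r = 0, 0.3 and 0.5) gives 89.5% to 91.3%. The result is therefore about 90% under every combination tried. With the MANOVA condition included (r = 0, gating difference 0), 95% power needs 54 per group (95.0%; 53 per group gives 94.6%).

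**Step 5: where the loss arises.** Taken first, the Bonferroni step costs 95.1 − 91.4 = 3.7 points. The MANOVA condition then costs a further 2.0 points at r = 0, 1.2 at r = ±0.3 and 0.4 at r = ±0.5. On this ordering most of the loss is due to the correction. The two steps overlap, however. With the MANOVA condition kept and the follow-up run at an uncorrected 0.05, power would be 90.3% at r = 0, 91.9% at r = 0.3 and 94.0% at r = 0.5. Dropping the Bonferroni step alone would therefore not restore 95%.

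**The case against.** The strongest reply is that nothing is broken. The printed arithmetic is right for the test it names, about 90% is good power, and Section 3.8 itself quotes 90% and 80% for Research Questions 2 and 3. In detectable effect the shortfall is 0.06 (0.84 against 0.78 at 95%), and the type I error is not harmed. It can be added that the MANOVA alpha and the Bonferroni divisor are unprinted, and that the MANOVA condition costs almost nothing if the two outcomes are well correlated. All of this stands and bears on severity. It does not remove the mismatch: both procedures are printed for the same question, and the 95% belongs to the one that will not be run. The two assumptions are the natural reading of the text.

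Stronger readings are tempting, but the document does not support them.

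- *The primary contrast is compromised because age is left out of the main model.* Section 3.2 caps age at 69 on the ground that the measures change particularly after that age, and it targets recruitment to match the groups on age and gender. Section 3.7 compares age between groups, and Section 3.7.1 states that "Hypotheses 1, 2, 3 will be rerun with age included as a covariate". Nor can a gain in power from age adjustment be derived from the 0.78: that figure comes from a young-versus-older contrast and does not give the share of variance that age explains in an 18–69 sample. Nothing in the text supports adjusting for gender.
- *The MANOVA will lose participants who lack one of the two measures.* Both are taken before the task in the first session, and Section 3.8 says "Dropout is not expected to impact Research Question 1a or 1b". No figure in the document contradicts this, and missing-data handling may be left to the analysis plan.

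**Conclusion.** The point holds as an inconsistency between Sections 3.7 and 3.8. For the analysis as written, power for Research Question 1a at d = 0.78 and 44 per group is about 90%, not 95%, an overstatement of 4 to 6 points. This rests on a MANOVA alpha of 0.05, a Bonferroni divisor of 2 and, for the base case, no gating difference; the correlation between the outcomes hardly matters.

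Severity is moderate. A reader might infer that the study is underpowered or the sample size miscalculated. Neither follows: 44 per group is correct for the test assumed, and about 90% is adequate if 0.78 is the true effect. What is wrong is the power figure attached to the planned procedure.

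**What to change.** Either of two changes settles it.

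1. Keep the Hypothesis 1 analysis and restate in Section 3.8 that 44 per group gives about 90% power for Research Question 1a under the MANOVA and Bonferroni procedure. Print the MANOVA alpha, the Bonferroni divisor, and the gating effect and correlation assumed. The cost is one sentence and a less favourable figure.
2. To keep 95% with the same 2 × 44 = 88 participants, prespecify attenuation (1a) as the single primary comparison, tested directly at two-sided 0.05, and make gating (1b) and the MANOVA secondary. With one primary test, no correction is needed for it. This costs more than wording. The abstract frames the primary objective as somatosensory processing in general, so that statement would need narrowing, and in a registered report the change should be recorded before outcome data are examined.

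The first is the smaller change and is sufficient.

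### The 60% power quoted under 10% dropout for Research Questions 2 and 3 cannot be squared with the 90% and 80% quoted beside it

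*Protocol article*

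**What the plan says.** All the figures are in section 3.8 (Sample size) of the protocol article.

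- The sample size is set by Research Question 1a, a two-sided comparison of two independent means with an effect of 0.78 and 95% power, which "requires 44 participants per group (G*power 3.1.9.7").
- For Research Questions 2 and 3, two pairs of figures are given, both at a 5% alpha. The first pair reads: "power of 90% to detect an effect of 0.70 between two groups at two repeated time points". The second pair puts power at 80% for the smaller effect, 0.60.
- On dropout: "A dropout rate of 10% would mean that our power to detect these effect sizes decreases to 60" per cent.

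The section says that dropout should not touch Research Questions 1a and 1b, which use first-session data, but may affect the questions that need a second visit. Section 3.5 then excludes participants who do not complete the cognitive task from Research Questions 2 to 4. The text gives no within-person correlation and no derivation of the 60%, only a link to code.

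**The concern.** A loss of 10% of participants is small. Power depends on the square root of the sample size, so such a loss should cost a few percentage points, not 20 or 30. It is also odd that two effect sizes with different starting powers should end at the same figure.

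The sentence matters for interpretation. Research Questions 2 and 3 depend on second-session data, and a reader who meets a null result there will turn to this sentence to judge how informative it is. As printed, it says that ordinary dropout leaves these questions badly underpowered. Either that is untrue, or the 90% and 80% are. The reader cannot tell which.

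**Working it through.** **Inputs from section 3.8.** 44 per group; alpha 0.05; effects 0.70 and 0.60 with stated powers 90% and 80%; dropout 10%, so 44 × 0.9 = 39.6, that is 39 or 40 per group. Two-sided testing is stated for Research Question 1a ("non‐directional two‐tailed hypothesis") and assumed here for 2 and 3. One-sided tests would give 94.7% and 87.4% at 44 per group, which do not match the stated 90% and 80%.

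**Step 1: reproduce the plan's starting figures.** For two groups of n, the noncentrality is d × √(n/2) with 2n − 2 degrees of freedom, and power comes from the noncentral t distribution.

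| Effect d | Noncentrality at n = 44 | Power | Stated |
|---|---|---|---|
| 0.78 (RQ 1a) | 0.78 × √22 = 3.66 | 95.1% | 95% |
| 0.70 | 0.70 × √22 = 3.28 | 90.1% | 90% |
| 0.60 | 0.60 × √22 = 2.81 | 79.5% | 80% |

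The 90% and 80% reproduce. They also arise from a pre-to-post change score with a within-person correlation of 0.5, because the standardised effect is d / √(2(1 − 0.5)) = d.

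**Step 2: apply 10% dropout.**

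| Effect d | n = 40 | n = 39.6 | n = 39 | Stated |
|---|---|---|---|---|
| 0.70 | 87.1% | 86.8% | 86.3% | 60% |
| 0.60 | 75.5% | 75.1% | 74.4% | 60% |

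**Step 3: repeat without assuming a test or correlation.** Any within-person correlation is already contained in the stated powers. In the normal approximation, a stated power P implies noncentrality 1.960 + z(P), and keeping 90% of participants multiplies it by √0.9 = 0.9487.

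- From 90%: 1.960 + 1.282 = 3.242; × 0.9487 = 3.075; − 1.960 = 1.115; power 86.8%.
- From 80%: 1.960 + 0.842 = 2.802; × 0.9487 = 2.658; − 1.960 = 0.698; power 75.7%.

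**Step 4: look for a reading that gives 60%.**

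| Reading | Effect 0.70 | Effect 0.60 |
|---|---|---|
| All dropout in one group (44 v 35) | 86.3% | 74.4% |
| 10% lost twice (81% retained, as in step 3) | 83.1% | 71.3% |

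By the t-test, 60% needs about 21 per group for 0.70 (1 − 21/44 = 52% loss). For 0.60 it needs 28.2, or 29 in whole participants (36% or 34% loss).

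Change scores with low correlation come close to 60% at 40 per group: 59.0% for 0.70 with correlation 0, and 58.1% for 0.60 with correlation 0.25. At 44 per group, however, they give only 63.1% and 62.3%, so they contradict the stated 90% and 80%.

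**Step 5: one value for two effects.** With the same design, n and alpha, noncentrality is proportional to the effect. Power of 60% means noncentrality 1.960 + 0.253 = 2.213.

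- If 0.70 had 60%, then 0.60 would have 2.213 × 0.60/0.70 = 1.897; − 1.960 = −0.063; power about 47%.
- If 0.60 had 60%, then 0.70 would have 2.213 × 0.70/0.60 = 2.582; − 1.960 = 0.622; power about 73%.

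**The case against.** The strongest reply is about weight. The study is sized on Research Question 1a, which reproduces and which the plan expects dropout not to affect. The 60% sets no recruitment target, inflation factor, analysis or decision rule. If the 90% and 80% are right, the error is conservative. All of this stands, and it limits the importance of the point.

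A second reply is that the explanation may lie in the linked code, which was not available for this check. That could show where the 60% came from. It could not reconcile it with the other two figures, since step 3 uses only the printed powers and the printed dropout rate.

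Three stronger readings are tempting but are not supported:

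- **That the design gives 87% and 75% outright.** Those values hold only if the 90% and 80% are correct. The plan describes two repeated time points and linear mixed models without giving the correlation. A change score with an assumed correlation of 0.4, for instance, goes from 84.2% to 80.6% and from 71.9% to 67.7%.
- **That a group-difference power is irrelevant to Hypotheses 2 and 3.** Group is a named predictor with a fixed effect in both models (section 3.7), so the figure does match one test in each. It does not cover the continuous predictors in either hypothesis, or the fatigability interactions, which appear only in Hypothesis 2.
- **That the closing statement, "adequately powered to detect correlations of 0.50 and 0.40, respectively", is also an error.** The sentence assigns the two values to Research Questions 2 and 3 but does not define them. They could be within-person or between-variable correlations. That is missing detail in a condensed article that points to code, and it does not show that the statement is wrong.

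**Conclusion.** The 60% is inconsistent with the 90% and 80% printed just before it. Taking those two as given, 10% dropout leaves about 87% for an effect of 0.70 and about 75–76% for 0.60, a fall of about 3 to 5 points, not the 30 and 20 implied. This assumes that noncentrality scales with the square root of the number retained and that 10% means a tenth of participants. It does not depend on the within-person correlation. That a single figure cannot hold for both effects follows from the different starting powers alone.

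The documents do not show which of the printed figures is the mistaken one. The 90% and 80% reproduce under a simple two-group comparison, which points to the 60%, but that is an inference.

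The importance is moderate. A reader might infer that the trial's sample size is unsound or that a figure it relies on has failed; the documents do not support that, because the error is confined to secondary questions and leaves the 44 per group unchanged.

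**What to change.** Recompute the dropout sentence in section 3.8 and replace the single 60% with a separate power for each effect size, stating the retained n, the test and the within-person correlation used. If the 90% and 80% are confirmed, the values at about 40 per group are about 87% (0.70) and about 75% (0.60). If the recalculation shows that the 60% came from a sound calculation on other assumptions, correct the 90% and 80% instead.

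Add one sentence saying that these powers refer to the group effect and do not extend to the continuous predictors in Hypotheses 2 and 3 or to the fatigability interactions in Hypothesis 2.

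The cost is a rerun of the existing power code and an edit to the text. Sample size, recruitment and analyses do not change.

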### Timeline

3.9

July 2024–April 2025: recruitment and data collection.

April 2025–May 2025: processing of data.

May 2025–June 2025: collating of results.

June 2025–August 2025: submission of Stage 2 registered report.
